#### **1.2.4 Rationale for Route of Administration**

PR006A will be delivered via a single suboccipital injection into the cisterna magna. This delivery method was chosen because in NHP studies it has been shown to result in broad biodistribution and cellular transduction throughout the brain ([Hinderer et al 2014](#); [Sorrentino et al 2016](#); [Hinderer et al 2018](#); [Hordeaux et al 2018](#); [Ohno et al 2018](#)).

Furthermore, CNS transduction is less likely to be affected by the presence of existing or elicited AAV9 neutralizing antibodies in the periphery compared to an intravenous route of administration ([Samaranch et al 2012](#); [Gray et al 2013](#); [Hinderer et al 2014](#); [Meyer et al 2015](#); [Hinderer et al 2018](#)). The procedure will be performed by an interventional radiologist or neurosurgeon who has experience with the procedure and using imaging guidance (with computed tomography [CT] fluoroscopy or 3-dimensional intraoperative imaging) while the patient is under general anesthesia or deep sedation.

### 1.2.5 Rationale for Dosing

The dose rationale is based on published human clinical, biomarker, and genetic data on *GRN* mutations and their causative effects in FTD; nonclinical efficacy, biodistribution, and safety results obtained in a mouse model of FTD-GRN; and biodistribution and safety results obtained in NHP studies.

Patients with FTD-GRN carry a germline mutation in 1 of the 2 chromosomal alleles of the *GRN* gene, resulting in a lifelong reduction of CSF and blood PGRN levels by approximately 50%. The goal of the PR006A therapy is to restore CNS PGRN levels as measured in the CSF. Our hypothesis is that restoring CNS PGRN to a normal level, or higher, will translate into a slowing or halting of clinical progression of the disease and potentially improvement of ongoing symptoms.

The starting dose of  $3.5 \times 10^{13}$  vg translates to a dose of  $2.7 \times 10^{10}$  vg/g brain weight, assuming an adult brain mass of 1.3 kg ([Hakim and Mathieson 1979](#)). In the *Grn* KO mouse studies,  $2.7 \times 10^{10}$  vg/g brain weight was the lowest dose tested that resulted in efficacy across the multiple key endpoints. In the multidose study, PR006A treatment resulted in a dose-dependent brain transduction of the *GRN* transgene and dose-dependent expression of progranulin mRNA and PGRN.

Equally important, the dose of  $2.7 \times 10^{10}$  vg/g brain weight improved the expression of several neuroinflammatory markers including the mRNA-level specific markers *Tnfa* and *Cd68* and significantly reduced the accumulation of lipofuscin in the brain, which is a pathologically relevant endpoint. Similar effects were also observed at the higher dose level.

Therefore, based on the results of *Grn* KO mouse efficacy study, a PR006A dose of  $2.7 \times 10^{10}$  vg/g brain would be predicted to increase brain PGRN levels to approximately a normal level and ameliorate essential pathological features seen in FTD-GRN, such as neuroinflammation and lipofuscin deposition, in FTD-GRN patients.

Regarding safety, no adverse findings were observed in the 6-month GLP study performed in NHPs administered PR006A at the dose levels of  $6.5 \times 10^9$  vg/g brain and  $6.5 \times 10^{10}$  vg/g brain. Furthermore, no PR006A-related safety findings were observed in the mouse studies up to the highest tested dose level of  $2.7 \times 10^{11}$  vg/g brain. The GLP NHP study establishes a

safety margin of 2.4x to the starting clinical dose; the *Grn* KO mouse studies establishes a safety margin of 10x to the starting clinical dose.

The GLP NHP study also served to evaluate biodistribution and transgene expression following ICM administration. ICM administration of PR006A resulted in widespread and broad transduction of the human *GRN* transgene in the brain and peripheral organs and in a dose-dependent increase in gene expression. *GRN* mRNA levels were elevated in all brain areas and peripheral tissues with positive transduction. Progranulin levels were measured in the CSF with an experimental method detecting both NHP and human PGRN. Treatment with the lower dose of PR006A ( $6.5 \times 10^9$  vg/g) and higher dose ( $6.5 \times 10^{10}$  vg/g) resulted in a 34% and 119% increase, respectively, in CSF PGRN compared to levels measured in control NHPs. The NHP biodistribution and *GRN* expression results provide further support for the efficacy of PR006A treatment and for the starting clinical dose, which is between the 2 dose levels tested in this NHP study.

The interspecies dose comparisons above are based on brain weight (vector genomes of PR006A per gram brain weight). To further assure translation of mouse and NHP results to dosing in patients and taking into account both the size of the brain and the route of administration, biodistribution observed in the 2 species was compared. In the mouse model, ICM administration of the mid dose of  $2.7 \times 10^{10}$  vg/g brain of PR006A resulted in brain vector genome exposure levels of  $3.2 \times 10^3 \pm 0.9 \times 10^3$  vg/ $\mu$ g DNA (mean  $\pm$  standard error of the mean) at Day 90. In NHPs, ICM administration of  $6.5 \times 10^9$  vg/g and  $6.5 \times 10^{10}$  vg/g of PR006A resulted in brain vector genome exposure of, respectively,  $7.5 \times 10^2 \pm 3.9 \times 10^2$  vg/ $\mu$ g and  $2.9 \times 10^4 \pm 1.3 \times 10^4$  vg/ $\mu$ g DNA (pooled data of all brain areas; mean  $\pm$  standard error of the mean) in the Day 183 cohort. These results support that interspecies dose comparisons based on vector genomes per gram brain weight are appropriate for selection of the human starting dose.

Sequential escalation to the mid-dose ( $7.0 \times 10^{13}$  vg) [REDACTED] level cohorts will occur in conjunction with iDMC recommendation, who will review pertinent safety, biomarker, and clinical data. These dose levels are a 2x [REDACTED] increase over the starting dose level.

During the conduct of the PRV-FTD101 clinical study, the Sponsor will also perform review of biomarker data at regular intervals. Based on this review and in consultation with iDMC, a

decision to suspend further enrollment in one cohort and start enrollment in the next higher dose cohort may be taken. A minimum of 3 patients in each cohort must be dosed prior to effectuating dose escalation.

In summary, the clinical starting dose of  $2.7 \times 10^{10}$  vg/g brain is predicted to be well tolerated, increase PGRN levels in the CNS, result in improvements of FTD-GRN pathology, and therefore potentially be clinically beneficial in FTD-GRN patients.

Refer to the investigator's brochure (IB) for a detailed description of the PR006A nonclinical data.

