### 1.2.3 Rationale for Staggering of Patient Enrollment

Based on available nonclinical data, no specific safety signals are anticipated in humans, other than potential risk for liver enzyme elevations related to AAV9-capsid-specific T-cell responses observed in previous human studies with AAV9 vectors ([Mendell et al 2017](#)). In order to monitor for any unexpected safety events in humans, including but not limited to potential transitory liver enzyme elevations, in each cohort, enrollment will be staggered by at least 8 weeks between the first 2 patients and then at least 8 weeks between the second patient and the remaining 3 patients of the cohort to permit review of safety, tolerability, immunogenicity, and, to the extent available, efficacy by the iDMC, who will ultimately provide a recommendation on further dosing. This 8-week monitoring period was established to capture the reported time-frame for liver enzyme elevations caused by T-cell responses, which were observed at approximately 3 weeks post-dosing ([Mendell et al 2017](#)). It also ensures the iDMC will have appropriate biomarker and safety data from the Month 2 visit to make their recommendation. Since presumably, CSF inflammatory changes occur between 1 and 2.5 months post-dosing, at least 8 weeks after the second staggered patient is dosed in Cohort 1, the iDMC will review all available safety, tolerability, immunogenicity, and, to the extent feasible, efficacy results from the first 2 patients in this cohort (dosed in a staggered manner). At the recommendation of the iDMC, the Sponsor will decide whether to dose the remaining 3 patients in Cohort 1 (low dose) without staggering and in parallel begin staggered enrollment in the mid-dose cohort (Cohort 2).

Escalation to the mid-dose ( $7.0 \times 10^{13}$  vg) [REDACTED] level cohorts will be based on iDMC recommendation, assessments of safety and biomarker data from the clinical PR006A low- and mid-dose cohorts, as well as technical feasibility (e.g., the ability to obtain sufficient concentrations of PR006A within the limitations of injectate volume).

Once enrollment of at least 2 patients in the low-dose cohort is complete and at least 8 weeks have elapsed after the second patient is dosed, the iDMC will review cumulative tabulated

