data from the low-dose cohort and recommend whether or not to initiate dosing in the mid-dose cohort. The mid- [REDACTED] dose cohorts will utilize the same approach (staggered patients followed by unstaggered patients) as the low-dose cohort. The same iDMC data review process will be followed once at least 2 patients have enrolled in the mid-dose cohort and at least 8 weeks have elapsed after the second patient is dosed, [REDACTED]  
[REDACTED]

The Sponsor will perform 3 formal interim analyses: 1) after all patients complete 12 months of treatment in Cohort 1; 2) after all patients complete 12 months of treatment in Cohort 2; [REDACTED]. Additionally, the Sponsor will perform a review of biomarker data at regular intervals. Based on the review of data through Month 2 in at least 2 patients and in consultation with the iDMC, a decision will be made to continue or suspend enrollment in any enrolling cohorts and to start enrollment in the subsequent cohort (i.e., dose escalate). A decision to dose escalate will be based on data from at least 2 patients from the concurrent cohort. However, all cohorts will enroll a minimum of 3 patients, unless enrollment is terminated due to safety concerns or based on biomarker review this dose is considered to be non-efficacious. In all other circumstances, the full cohort of 5 patients will be enrolled. Additional interim analyses may be performed during the follow-up period (post-Year 1) based on Sponsor's discretion.

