##### **3.1.1 Year 1**

Fifteen patients will be administered a one-time dose of PR006A, suboccipitally injected into the cisterna magna by an interventional radiologist or neurosurgeon.

In each cohort, enrollment will be staggered by at least 8 weeks between the first 2 patients and then an additional 8 weeks between the second patient and the remaining 3 patients of the cohort to permit review of safety, tolerability, immunogenicity, and, to the extent available, efficacy by the iDMC, who will ultimately provide a recommendation on further dosing. At least 8 weeks after the second staggered patient is dosed in Cohort 1, the iDMC will review all available safety, tolerability, immunogenicity, and, to the extent feasible, efficacy results from the first 2 patients in this cohort (dosed in a staggered manner). At the recommendation of the iDMC, the Sponsor will decide whether to dose the remaining 3 patients in Cohort 1 (low dose) without staggering and in parallel begin staggered enrollment in the mid-dose cohort (Cohort 2).

Cohort 2 will enroll 5 patients to receive the mid-dose ( $7.0 \times 10^{13}$  vg) of PR006A, and

[REDACTED]. The design for Cohorts 2 [REDACTED] enrollment is the same as for Cohort 1.

If a decision is made to not open or to limit enrollment into a cohort (i.e., Cohort 2 and/or [REDACTED] due to safety or tolerability reasons, the unenrolled subjects may be re-allocated to a lower dose level cohort.

One loading dose of 6 mg oral sirolimus will be administered at Day -1, as well as a single dose of 1 g IV methylprednisone at Day 0. A concomitant maintenance dose of 2 mg/day sirolimus will be administered orally for 90 days starting at Day 0 which will then be tapered over the ensuing 15 to 30 days. The maintenance dose is administered to achieve a trough sirolimus concentration of 4 ng/mL (range 2 to 8 ng/mL). One day after treatment with PR006A, patients will start prednisone 30 mg orally for 14 days, followed by a 7-day taper. At the Investigator's discretion, adjustments of dose and duration are permitted.

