During the dose-escalation period of the study, the Sponsor will perform a review of biomarker data at regular intervals. Based on the review(s) and in consultation with the iDMC, a decision may be taken to suspend enrollment in the low-dose cohort and start enrollment in mid-dose cohort or suspend enrollment in the mid-dose cohort [REDACTED], depending on the stage of dose escalation. A decision to dose escalate will be based on data from at least 2 patients from the concurrent cohort. However, all cohorts will enroll a minimum of 3 patients, unless enrollment is terminated due to safety concerns or based on biomarker review this dose is considered to be non-efficacious. In all other circumstances, the full cohort of 5 patients will be enrolled.

An iDMC consisting of clinicians and a biostatistician otherwise unaffiliated with the conduct of the study will conduct a review of the safety, tolerability, immunogenicity, and available efficacy data in accordance with the charter. The iDMC will assess safety variables as listed for the primary safety endpoints outlined in [Section 2](#).

The Sponsor will perform 3 formal interim analyses: 1) after all patients complete 12 months of treatment in Cohort 1; 2) after all patients complete 12 months of treatment in Cohort 2; [REDACTED]. Additionally, the Sponsor will perform a review of biomarker data at regular intervals. Based on the review of data through Month 2 in at least 2 patients and in consultation with the iDMC, a decision will

be made to continue or suspend enrollment in any enrolling cohorts and to start enrollment in the subsequent cohort (i.e., dose escalate). A decision to dose escalate will be based on data from at least 2 patients from the concurrent cohort. However, all cohorts will enroll a minimum of 3 patients, unless enrollment is terminated due to safety concerns or based on biomarker review this dose is considered to be non-efficacious. In all other circumstances, the full cohort of 5 patients will be enrolled.

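### Section 1.2.5 requires 3 patients dosed per cohort before escalation, while the synopsis and Sections 1.2.3, 3.1.1 and 11.1.1 let the next dose start after review of 2

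*Protocol*

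**What the plan says.** Section 1.2.5 (Rationale for Dosing) says that biomarker review, in consultation with the iDMC, may lead the sponsor to suspend enrolment in one cohort and start the next higher one. It then adds: "A minimum of 3 patients in each cohort must be dosed prior to effectuating dose escalation". No exception is given.

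Four other places describe escalation differently:

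- Section 3.1.1, with the same rule in the synopsis and Sections 1.2.3 and 11.1.1: "A decision to dose escalate will be based on data from at least 2 patients from the concurrent cohort".
- Section 3.1.1, on what may follow iDMC review of the first 2 patients; the synopsis and Sections 1.2.3 and 11.1.1 agree. The sponsor decides whether to "dose the remaining 3 patients in Cohort 1 (low dose) without staggering and in parallel begin staggered enrollment in the mid-dose cohort".
- Section 1.2.3, on the trigger for that review, with the interval counted from the second patient's dose: "Once enrollment of at least 2 patients in the low-dose cohort is complete and at least 8 weeks have elapsed after the second patient". As the outcome of that review, the iDMC must "recommend whether or not to initiate dosing in the mid-dose cohort".
- Section 1.2.3, on the sponsor's decision to escalate, repeated in the synopsis and Section 3.1.1: "Based on the review of data through Month 2 in at least 2 patients and in consultation with the iDMC".

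These sections also contain the number 3, but in another role: "However, all cohorts will enroll a minimum of 3 patients, unless enrollment is terminated due to safety concerns". The same sentence gives a second exception, for a dose that biomarker review judges non-efficacious.

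**The concern.** The escalation gate is a main safety control in this trial. It is a first-in-human study of a gene therapy given once, the mid dose is twice the starting dose, and Section 1.3 states that immunogenicity in humans is unknown. The iDMC, the sites and the ethics committees need one answer to a simple question: how many patients must have been dosed at the current level before anyone receives the next one?

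The protocol gives two. Section 1.2.5 answers 3, always. The other sections set a minimum of 2 with reviewed data, and no third dosed patient is required first. An escalation run exactly as Section 3.1.1 describes could later be recorded as a deviation from Section 1.2.5, and the two texts imply different numbers of exposed patients behind the first higher dose.

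**Working it through.** The gate is a stated rule, so there is no plan figure to reproduce. The only related arithmetic in the protocol, 3 cohorts × 5 patients = 15, agrees.

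**Step 1: the rules side by side**

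| Question | Section 1.2.5 | Synopsis, 1.2.3, 3.1.1, 11.1.1 |
|---|---|---|
| Patients with data behind the decision | not stated | at least 2 |
| Patients dosed before the higher dose starts | at least 3 | no number beyond the 2 reviewed |
| Role of the number 3 | condition on timing | minimum enrolment per cohort |
| Exceptions to 3 | none | safety; dose judged non-efficacious |

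**Step 2: one schedule tested against both**

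- Cohort 1, patient 1: week 0.
- Cohort 1, patient 2: 0 + 8 = week 8 at the earliest.
- iDMC review: 8 + 8 = week 16 at the earliest.
- After a favourable review, Cohort 1 patients 3 to 5 and Cohort 2 patient 1 may all proceed. No order between them is set.

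Suppose Cohort 2 patient 1 is dosed before Cohort 1 patient 3. The number dosed at the low level is then 2. The operative sections permit this. Section 1.2.5, read literally, does not, because 2 < 3.

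**Step 3: the early-suspension route**

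Suppose the 3-patient sentence in Section 1.2.5 governs only the case in which a cohort is suspended early on biomarker data. Section 3.1.1 describes that same route, again with data from at least 2 patients, and waives the floor of 3 if the dose is judged non-efficacious. After such a judgement with 2 patients dosed, Section 3.1.1 allows escalation and Section 1.2.5 blocks it. The narrow reading reduces the conflict but does not remove it.

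**Step 4: what 2 or 3 patients could show**

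The protocol gives no event rates, so those below are assumed. P(at least one event) = 1 − (1 − p)^n.

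| Assumed risk p | n = 2 | n = 3 |
|---|---|---|
| 10% | 1 − 0.9² = 19% | 1 − 0.9³ = 27% |
| 20% | 1 − 0.8² = 36% | 1 − 0.8³ = 49% |
| 30% | 1 − 0.7² = 51% | 1 − 0.7³ = 66% |
| 40% | 1 − 0.6² = 64% | 1 − 0.6³ = 78% |

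With no events, the one-sided 95% upper bound on the risk is 1 − 0.05^(1/n): 78% for n = 2 and 63% for n = 3.

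The n = 3 columns assume that the third patient is fully observed. Section 1.2.5 asks only that this patient be dosed. If dosing takes place just before escalation, the reviewed evidence is the same 2 patients under either rule. The true difference therefore lies between almost nothing and the differences shown.

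**The case against.** The strongest reply is that the two rules can be read together. Both numbers are minima: the decision rests on data from at least 2 patients, and it is put into effect once a third has been dosed. After the 2-patient review, the remaining Cohort 1 patients need no staggering, so a third can be dosed before the first Cohort 2 patient, and every passage is then met. This stands. A reader might infer from the contrast that no conduct can satisfy both texts; the documents do not support that. What remains is that the operative sections do not impose this order. They open both cohorts in parallel and let the iDMC recommend mid-dose dosing after 2 patients, with no mention of a third.

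A second reply is that the sentence in Section 1.2.5 follows directly on the early-suspension route and may apply only there. The placement supports this, but the wording refers to dose escalation in general, and Step 3 shows that the missing exceptions would still conflict.

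A third is that the number 3 is not peculiar to Section 1.2.5. That is correct: the synopsis and Sections 1.2.3, 3.1.1 and 11.1.1 all state a 3-patient minimum. There it concerns how many a cohort eventually enrols, not when the next level may start.

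Finally, the outlier is one sentence in a rationale section. The operative sections agree with each other, and iDMC review, 8-week staggering and the stopping rules apply as well. This limits the practical danger. It does not settle which sentence governs. The iDMC charter, which might, is not available.

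**Conclusion.** The point holds as an internal contradiction in a safety decision rule. Section 1.2.5 makes 3 dosed patients an unconditional requirement before escalation; the synopsis and Sections 1.2.3, 3.1.1 and 11.1.1 permit the next dose level to start with 2. This conclusion rests on the text alone.

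Its size is one dosed patient per escalation step. A reader might take the 36% against 49% contrast as the safety information lost under the 2-patient rule. The documents do not support that: the event rates are assumed, and the 3-patient values are upper limits because no follow-up of the third patient is required. The figures are illustrative only. Nor does the comparison show which rule is right; that is a matter for the sponsor and the iDMC.

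**What to change.** Reconcile the passages before the next escalation decision. State one escalation gate that specifies:

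- the number of patients who must have been dosed at the current level;
- the number who must have reviewed data, and through which visit;
- any exceptions;
- the route to which it applies: parallel opening, early suspension of a cohort, or both.

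Use identical wording in the synopsis and Sections 1.2.3, 1.2.5, 3.1.1 and 11.1.1, and check that the iDMC charter matches. If the sentence in Section 1.2.5 is meant only for early suspension, say so there and carry over whichever exceptions are intended. Stating beside the gate the upper bound on event risk that the chosen number can exclude would be a useful but optional addition.

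The cost is amendment wording; sample size and assessments need not change.

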### **Rationale for immunosuppressant regimen**

Intracisternal administration has been chosen to maximize the distribution of PR006A throughout the CNS and minimize systemic exposure to the viral capsid of AAV9 and the T-cell response, but inevitably there will be some escape of the virus out of the CSF and into the blood. In clinical studies, gene therapy candidates using AAV9 have been generally well-tolerated. Transient elevations in alanine aminotransferase (ALT) and/or aspartate aminotransferase (AST) levels, which respond to corticosteroid treatment, have been observed to occur approximately 3 weeks after treatment ([Mendell et al 2017](#)). Additionally, the second immunosuppressive agent, sirolimus, has been shown to suppress AAV-related and transgene protein expression-related immune responses in NHPs ([Mingozzi et al 2007](#); [Ramsingh et al 2018](#)), is reported to be beneficial in animal models of FTD ([Wang et al 2012](#)), and has a manageable safety profile which is considered steroid-sparing ([Pidala et al 2020](#)).

Therefore, in order to mitigate ALT and/or AST elevations, inflammatory changes in the CSF or other suspected immune system reactions, 1 loading dose of 6 mg oral sirolimus will be administered at Day -1, as well as a single dose of 1 g intravenous (IV) methylprednisone at Day 0. A concomitant maintenance dose of 2 mg/day sirolimus will be administered orally for 90 days starting at Day 0, which will then be tapered over the ensuing 15 to 30 days. The maintenance dose is administered to achieve trough levels of 4 ng/mL (range 2 to 8 ng/mL). One day after treatment with PR006A, patients will start prednisone 30 mg orally for 14 days followed by a 7-day taper.

At the Investigator's discretion, higher doses, a longer taper, or re-initiation of immunosuppressive treatment may be used (e.g., in cases of elevated AST or ALT, inflammatory changes in the CSF, or other suspected immune system reactions).

